### Data analysis

Summary tables for patient demographics as well as baseline and intervention characteristics will be provided. Further statistical analysis will be tailored for each of the study’s aims. The methods per aim are presented below, following the same order:

To identify risk factors associated with vessel perforations, we will, in the first stage, make comparisons between cases with and without perforation during thrombectomy for predefined risk factors. Statistical analyses will include paired samples *t*-test, Wilcoxon test, and chi-squared test or Fisher’s exact test. Furthermore, multivariable logistic regression models can be used to identify the association between multiple variables and the occurrence of vessel perforations.An exploratory analysis of the interventional image material in the central image analysis laboratory is planned. After reviewing the image material of approximately 20% of patients with explorative intention, imaging criteria will be defined with regard to possible mechanisms of vessel wall injury and distinct pathophysiological phenomena. These criteria will be used to classify the remaining 80% of patients. Due to the exploratory nature, no definitive statistical evaluation strategy can yet be determined.For this purpose, data-driven K-nearest neighbor clustering will be applied to identify different groups of similar patient characteristics. We will consider 2–4 clusters, and the distribution of the clusters will be inspected visually. After the identification of the clusters, we will compare the pathophysiological characteristics between the clusters.Patients with perforation will be divided into two groups: patients who received interventional hemostatic therapy after the perforation occurred—e.g., temporary intracranial balloon occlusion or permanent vessel occlusion with liquid embolization or coils—and patients who did not receive hemostatic therapy. Propensity score matching or inverse probability of treatment weighting will be used to control for the location of perforation and the flow rate of extravasation. The two groups will be compared with each other to identify differences in the duration of extravasation and in clinical outcomes. The appropriate statistical model will be used for each of the clinical outcomes (e.g., logistic regression model for binary outcomes and ordinal regression model for ordinal outcomes).Patients with perforation will be divided into two groups: patients in whom thrombectomy was continued after the perforation occurred and patients in whom the procedure was aborted. Propensity score matching or inverse probability of treatment weighting will be used to control for the amount of extravasation, stroke severity, occlusion location, collateral status, and other clinical outcome predictors. The two groups will be compared with each other to identify differences in clinical outcomes.The new insights on risk factors, mechanisms, and pathophysiology of vessel perforation will be gathered. An expert panel will discuss potential modifications to current thrombectomy workflows to reduce the risk of periprocedural perforation, both in response to specific patient-related risk factors (e.g., occlusion location and vessel tortuosity) and in general. No definitive statistical evaluation strategy can yet be determined.

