**Design:**

The Perforation EVents during ENdovascular Therapy for acute ischemic stroke (PREVENT) Registry is an international, multicenter, prospective, and retrospective study, collecting data on vessel perforations during thrombectomy. The registry aims to include 500 cases of vessel perforation and 500 matched controls without perforation. The collected data will consist of both tabulated data and periprocedural imaging, which is to be analyzed centrally by an imaging core laboratory. Data will be analyzed using a case–control method, employing both univariate and multivariate statistical analyses.

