**Discussion:**

Given the frequency and hyperacute nature of vessel perforations, a prospective randomized study is not feasible. This large, international registry provides a robust approach to collecting real-world evidence, reducing bias through multicenter data collection and case matching. The findings may help improve clinical decision-making and enhance patient safety during thrombectomy procedures.

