### Selection/treatment of subjects

Adult patients (≥18 years) who underwent thrombectomy for acute ischemic stroke on or after 1 January 2015 and experienced a periprocedural vessel perforation will be included. Vessel perforation is defined as contrast extravasation in at least one angiography series. Patients will be excluded if intracranial hemorrhage was present on pre-interventional imaging, if vessel wall damage was due to intracranial dissection without active contrast extravasation, if vessel perforation was due to the rupture of a pre-existing intracranial aneurysm (i.e., extravasation originates from an aneurysmal outpouching or dilation of an intracranial artery on the first run that demonstrates extravasation), or if vessel perforation led to the development of an arteriovenous fistula (e.g., carotid-cavernous fistula), but not to subarachnoid hemorrhage.

To evaluate risk factors that predispose patients to perforations, PREVENT is designed as a case–control registry. For the inclusion of each patient who experiences a perforation during thrombectomy, one matched patient of the same sex and similar age, with acute ischemic stroke due to vessel occlusion in the same vascular segment and treated at the same center, but without perforation, will be included.

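### Aim 1 matches controls 1:1 but lists chi-squared and Fisher's exact tests, which ignore the pairs, for categorical risk factors

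*Protocol article*

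**What the plan says.** The Selection/treatment of subjects section gives the reason for enrolling controls: "To evaluate risk factors that predispose patients to perforations, PREVENT is designed as a case–control registry". Each case brings in "one matched patient of the same sex and similar age, with acute ischemic stroke due to vessel occlusion in the same vascular segment", and the control must also be "treated at the same center, but without perforation, will be included". This is individual 1:1 matching on four factors. The target in the abstract's Design paragraph is 500 cases and 500 matched controls.

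The Data analysis section, under the first aim, then names the first-stage comparisons: "Statistical analyses will include paired samples *t*-test, Wilcoxon test, and chi-squared test or Fisher’s exact test". For the second stage it says that "multivariable logistic regression models can be used to identify the association between multiple variables and the occurrence of vessel perforations". It does not say whether that model is conditional or unconditional, or whether the matching factors enter it. The type of Wilcoxon test (signed-rank or rank-sum) is not stated either. The document attaches no significance level, power, effect size or exposure prevalence to aim 1.

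**The concern.** The same pairs are treated as dependent in one half of a sentence and as independent in the other. The t-test is paired. The chi-squared and Fisher's exact tests, which apply only to categorical factors, compare two independent groups, and neither McNemar's test nor any other paired categorical test is named.

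Matching in a case–control study makes controls resemble their cases on the matching factors and on whatever goes with them. If an exposure is correlated within pairs and the analysis breaks the pairs, the crude odds ratio is closer to 1 than the within-pair odds ratio, and the unpaired test uses too large a variance. The result is understated or missed risk factors rather than false ones. This matters because identifying risk factors is why controls are collected, and several candidates that the article lists (anesthesia, technique, device design, operator experience) are largely categorical and could plausibly differ between centers, center being a matching factor.

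**Working it through.** **Side by side.** Design: one control per case, same sex, similar age, same segment, same center. Analysis of continuous factors: paired t-test. Analysis of categorical factors: chi-squared or Fisher. Only the first test uses the pairs.

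**No stated figure to reproduce.** The 500 + 500 target carries no power inputs, so the check concerns the consequence of the stated tests.

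**Inputs.**
- From the article: n = 500 pairs.
- Assumed, because the article gives none: two-sided 5% level; true within-pair odds ratio (OR) 1.5; exposure prevalence 0.5 in controls; between-pair SD on the logit scale from 0 to 2.

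**Model.** For a pair with effect a ~ N(0, SD²), the control is exposed with probability p0 = expit(a) and the case with p1 = expit(a + ln OR). Averaging over a gives:
- P0 = E[p0] and P1 = E[p1]
- p10 = E[p1(1 − p0)] (only the case exposed) and p01 = E[p0(1 − p1)] (only the control exposed)
- d = p10 − p01 = P1 − P0
- crude OR = [P1/(1 − P1)] / [P0/(1 − P0)]; matched OR = p10/p01
- standard error of the difference, s = √[(p10 + p01 − d²)/n]
- McNemar power = Φ{(d − 1.96√[(p10 + p01)/n]) / s}
- chi-squared power on the same paired data = Φ{(d − 1.96√[2p̄(1 − p̄)/n]) / s}, with p̄ = (P1 + P0)/2

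**Worked case, SD 2.** P0 = 0.5000, P1 = 0.5611, p10 = 0.1834, p01 = 0.1223, d = 0.0611.
- Crude OR = 0.5611/0.4389 = 1.28. Matched OR = 0.1834/0.1223 = 1.50.
- s = √[(0.3057 − 0.0037)/500] = 0.0246.
- McNemar threshold 1.96√(0.3057/500) = 0.0485, so power = Φ(0.51) = 70%.
- Chi-squared threshold 1.96√(0.4981/500) = 0.0619, so power = Φ(−0.03) = 49%.

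**Range over SD (true OR 1.5, prevalence 0.5).**

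| SD | within-pair phi | crude OR | matched OR | chi-squared power | McNemar power | actual type I error of chi-squared |
|---|---|---|---|---|---|---|
| 0 | 0.00 | 1.50 | 1.50 | 89% | 89% | 5.0% |
| 0.5 | 0.06 | 1.47 | 1.50 | 86% | 87% | 4.4% |
| 1 | 0.17 | 1.40 | 1.50 | 77% | 82% | 3.1% |
| 2 | 0.39 | 1.28 | 1.50 | 49% | 70% | 1.2% |

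**Other assumed inputs.** With prevalence 0.3 and OR 1.5 the pattern is the same: at SD 2 the crude OR is 1.29, with power 45% against 65%. With OR 2.0 and prevalence 0.3 to 0.5 the power loss is at most about 4 points up to SD 2, although the crude OR still falls to 1.52–1.53. With OR 2.0 and prevalence 0.1, at SD 2, the crude OR is 1.62 and power is 74% against 84%.

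**Multivariable model.** A simulation of 500 pairs (200 replicates; 25 centers, four segments, sex and age all assumed; true OR 1.5) gave:
- logistic regression without the matching factors: OR 1.38, power 69%
- logistic regression with the matching factors as covariates: OR 1.51, power 76.5%
- conditional analysis: OR 1.49, power 75.5%

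With 200 replicates the standard error of a power near 76% is √(0.76 × 0.24/200) = 3 points, so the last two are indistinguishable.

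**The case against.** A condensed article may leave model details to an analysis plan. The univariable tests are only a first stage, their list is open, and no test is tied to a variable type. The error is conservative, and the matching is kept in the data, so a paired analysis stays possible. All of that stands as an argument about weight. It does not remove the point, because the article does not leave the categorical tests open: it names two that do not fit the design. Nor can the chi-squared test readily be read as McNemar's, since Fisher's exact test is offered as its alternative and is itself an independent-groups test.

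Three stronger readings are tempting and are not supported:

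- A reader might infer that the multivariable analysis will be ordinary logistic regression ignoring the pairs. The text says only that logistic models can be used. Conditional logistic regression is such a model, and an unconditional model with the matching factors as covariates did as well in the simulation.
- A reader might infer that bias and lost power are certain. Both are nil when the exposure is unrelated to the matching factors and small at a within-pair phi near 0.05.
- A reader might take strong between-center variation in anesthesia or devices as given. The article names these as possible risk factors but gives no figures on how they vary by center, so this is an assumption.

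**Conclusion.** The point holds for the categorical tests: as written, aim 1 respects the pairs for continuous factors (at least through the t-test) and not for categorical ones. The form of the logistic model is unstated and therefore needs to be specified; it is not shown to be wrong.

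The size depends on a within-pair correlation that the article does not report. Under the assumptions above, the loss at a true odds ratio of 1.5 runs from nothing (SD 0), through about 5 points of power and a crude odds ratio of 1.40 (SD 1), to about 21 points and 1.28 (SD 2). Stronger effects of common exposures lose little power, but their odds ratios are still understated. The claim in the abstract's discussion of "reducing bias through multicenter data collection and case matching" is best served by an analysis that uses the matching. I would rate this as should-fix, not must-fix: it does not create false risk factors, and the matched data allow a paired analysis at any time.

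**What to change.** In the aim 1 text:

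- Replace the chi-squared and Fisher's exact tests with McNemar's test for binary factors (exact version when discordant pairs are few) and the Stuart-Maxwell or Bowker test for factors with more than two categories.
- State that the Wilcoxon test is the signed-rank test.
- Specify the multivariable model as either conditional logistic regression on the matched pairs, with age as a covariate because age is only similar within pairs, or unconditional logistic regression that includes all four matching factors (sex, age, segment, center).

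The cost is a change of wording, with no new data and no change to enrollment. The one downside is that pairs in which either member lacks the exposure value drop out of the paired analyses unless the value is imputed, so the handling of missing exposures should be stated with the tests.

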**Objectives:**

The primary objectives of this study are to (1) identify risk factors for vessel perforation, (2) explore the underlying pathophysiology, (3) develop a classification system for vessel perforations, (4) compare different hemostatic treatment strategies, (5) evaluate the impact of continuing versus aborting thrombectomy after perforation, and (6) propose a safety-optimized thrombectomy technique.

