Which risk factors are associated with the occurrence of vessel perforations during thrombectomy?Is it possible to identify distinct mechanisms of vessel perforation? Is it possible to describe pathophysiological phenomena associated with vessel perforation?Are there groups of perforations that can be distinguished in terms of risk profiles and the need for urgent complication management, on the basis of which a classification system can be created? If so, can a pathophysiological explanation be found for the differences between these groups?In patients with ongoing contrast extravasation, which individuals should receive endovascular therapy to achieve hemostasis? How do specific hemostatic strategies compare to others regarding efficacy and safety?In patients in whom ongoing contrast extravasation has stopped, should thrombectomy be continued, or should the procedure be aborted?Based on the insights gained from PREVENT, is it possible to design a safety-optimized thrombectomy technique that may be used if patient-related risk factors imply an increased risk of vessel perforation?

Figure 1 shows the aims of the PREVENT registry.

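### Aim 3 names K-nearest neighbor, a supervised classifier, to find 2–4 unlabelled groups, and the range leaves no room for the answer that no distinct groups exist

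*Protocol article*

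**What the plan says.** The protocol article lists six primary objectives. The third is to "develop a classification system for vessel perforations" (abstract, Objectives). The Design section phrases it as a question: "Are there groups of perforations that can be distinguished in terms of risk profiles and the need for urgent complication management". It makes the follow-on question, about a pathophysiological explanation, conditional on such groups being found.

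The Data analysis section commits this aim to one method: "data-driven K-nearest neighbor clustering will be applied to identify different groups of similar patient characteristics". It continues: "We will consider 2–4 clusters, and the distribution of the clusters will be inspected visually". The use of the result is then given: "After the identification of the clusters, we will compare the pathophysiological characteristics between the clusters".

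On size, the abstract says: "The registry aims to include 500 cases of vessel perforation and 500 matched controls without perforation".

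The article names no other algorithm and no other check on the clusters for this aim. For aims 2 and 6 it says that the statistical strategy is still open. For aim 3 it does not.

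**The concern.** Two things in the stated text do not fit the aim.

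First, the method. K-nearest neighbor predicts the class or value of a case from its K closest cases whose class or value is already known. Aim 3 has no known classes, because the classes are what the analysis is meant to find. An analyst who follows the text cannot run it as written. One who departs from it must choose an algorithm that the published plan does not name. If that choice is made after the data have been seen, the classification depends partly on the analyst's discretion.

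Second, the range. The question can be answered with no, but 2 to 4 clusters does not include one. The likely substitutes, partitioning methods, deliver whatever number is requested. The registry could then publish a classification of perforations that reflects the request and not the patients.

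**Working it through.** The document gives no figure to reproduce for this aim. The check has three steps.

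**1. Definition against text.**

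| What aim 3 needs | What K-nearest neighbor offers |
|---|---|
| Groups found without labels | A prediction from labelled cases |
| A number of groups from 2 to 4 | K, a number of neighbours; no parameter for the number of groups |
| A possible answer that no groups exist | Not applicable: classes are given in advance |

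**2. Could K be read as a number of groups after all?** One lenient reading joins each patient to the K nearest patients and counts the separate connected parts of that graph. Simulation inputs: 500 patients (the target number of cases, from the abstract) and, by assumption, 6 independent standard normal variables and 100 runs per setting. In the structured setting there are three true groups, each shifted by 4 standard deviations on one of the first three variables.

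| Data | K = 2 | K = 3 | K = 4 |
|---|---|---|---|
| No groups: median parts (range) | 1 (1–4) | 1 (1–1) | 1 (1–1) |
| Three true groups: median parts (range) | 2 (1–4) | 1 (1–2) | 1 (1–2) |

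K does not set the number of groups. With three well-separated groups present, K = 3 gave a median of one part.

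**3. What would a partitioning method show if there were no groups?** The inputs are 500 patients, 6 independent standard normal variables, no true groups, and k-means with 50 runs for each k. Cluster sizes were sorted within each run and averaged.

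| k requested | Mean sizes | Smallest and largest share | Equal share |
|---|---|---|---|
| 2 | 233 / 267 | 233/500 = 46.6%; 267/500 = 53.4% | 50% |
| 3 | 151 / 167 / 182 | 151/500 = 30.2%; 182/500 = 36.4% | 33.3% |
| 4 | 107 / 119 / 131 / 143 | 107/500 = 21.4%; 143/500 = 28.6% | 25% |

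The method returned the requested number of clusters, and their sizes were close to equal. Balanced sizes are therefore no evidence that groups exist.

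k-means is used here only as a plausible substitute, since the article does not name it. The simulation looked at sizes. If the visual inspection means a plot of patients by cluster, an attentive reader might notice that there are no gaps. The stated range would still oblige the analysis to report at least two groups.

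**The case against.** The strongest reply is that this is loose wording in a condensed article. The words around the method name make the unsupervised intent plain, and clustering on a nearest-neighbour graph (spectral clustering, for example) is an established family in which the number of clusters can be set. Variable lists, tuning and selection rules commonly sit in a full protocol or SAP, which is not shown. The aim is descriptive, no confirmatory test is attached to it, and the planned analyses for aims 4 and 5 do not use the clusters.

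Much of this stands. Graph-based clustering means that it would be too strong to call the task impossible for any nearest-neighbour method; the article simply does not describe one. The missing variable list is not a fault. But the method name and the range starting at 2 are statements in the text, not omissions, and each conflicts with the aim it serves.

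A reader might also infer more than the document supports:

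- **That the later comparison is circular.** Variables that formed the clusters will differ between them almost by construction. The article, however, clusters on patient characteristics and then compares pathophysiological ones. In a simulation of 300 runs (k-means, k = 3, 500 patients, 6 independent inputs), variables independent of the inputs and not used for clustering gave p < 0.05 in 5.4% of tests, about the nominal rate. Circularity arises only if the two sets overlap, which the text neither states nor rules out.
- **That visual inspection selects the number of clusters.** The text says only that the distribution is looked at. It is the only check named, but it is not called a selection rule.
- **That perforation features such as flow rate are excluded as inputs.** The article lists no inputs. Grouping by patient profile and then looking for a pathophysiological explanation is consistent with the order of the research question.
- **That the method cannot handle mixed data.** This would be an objection to k-means, which the article does not name.

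**Conclusion.** The point holds in two parts. As named, the method for aim 3 does not yield the groups described, because it is supervised, needs labels that do not exist, and has no parameter for the number of clusters. Separately, the range of 2 to 4 excludes the answer that no distinct groups exist, although the research question allows it. Cluster sizes alone would not expose this: with one homogeneous population of 500 and three clusters requested, the average split was about 151/167/182.

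The first part rests on the definition of the method, and the second on the stated range. The size figures rest on assumed data (6 independent normal variables) and on k-means as a stand-in. They illustrate behaviour and do not estimate an error rate for this registry.

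The point should be fixed, because classification is a listed primary objective and this is its only stated statistical method. It does not affect data collection or the other aims' stated analyses.

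**What to change.** Before the clustering is run:

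1. Replace the term K-nearest neighbor clustering with an actual unsupervised method that handles the data types collected. Examples are latent class analysis for mixed variables, or k-medoids on Gower distance. If clustering on a nearest-neighbour graph was meant, say so and describe it.
2. Consider 1 to 4 classes instead of 2 to 4.
3. Judge the number by a criterion that can return one class, for example BIC with latent class analysis or the gap statistic with k-medoids. Add a bootstrap check of cluster stability and keep the visual inspection as a supplement.
4. State that the later comparison of pathophysiological characteristics is limited to variables not used to form the clusters.

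The cost is a change of wording and modest programming, with no new data. The scientific cost is that the analysis may report that no distinct groups exist. That would be a valid answer to the question asked.

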## Methods and analysis

### Design

The Perforation EVents during ENdovascular Therapy for acute ischemic stroke (PREVENT) Registry is an international, multicenter, prospective, and retrospective observational study collecting data on vessel perforations during thrombectomy.

Data collection includes the following:

Patient baseline data (e.g., age, sex, pre-stroke modified Rankin Scale (mRS), pre-stroke anticoagulation or platelet therapy, and others).Data on the initial ischemic event (e.g., NIHSS at admission, number and location of vessel occlusions, TOAST classification [trial of ORG 10172 in Acute Stroke Treatment], imaging features related to clot composition, intracranial atherosclerotic disease (ICAD) or primary intracranial dissection, non-interventional stroke management, and other relevant factors).Details on circumstances and technique of the thrombectomy (e.g., anesthesiological management, type of aortic arch, cervical stenosis, thrombectomy technique, design and dimensions of the thrombectomy devices, operator experience, and others).Hemostatic therapy (e.g., non-endovascular hemostatic measures such as lowering of the systemic blood pressure or medication with coagulation effects, endovascular hemostatic measures including timing, exact mechanism, effectiveness, and other relevant factors).Outcome measures (e.g., functional outcomes including mRS at 90 days, and imaging outcomes including recanalization status, volume of intracranial hemorrhage, and other relevant factors).

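### Aim 3 names a supervised classifier, K-nearest neighbor, as its clustering method, so the text specifies no procedure that yields the 2–4 clusters behind the classification system

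*Protocol article*

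**What the plan says.** The abstract of the protocol article lists six primary objectives. The third is to "develop a classification system for vessel perforations". The list of study questions under Design asks whether distinguishable groups of perforations exist, "on the basis of which a classification system can be created".

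The third item under Data analysis gives the method: "data-driven K-nearest neighbor clustering will be applied to identify different groups of similar patient characteristics". It continues: "We will consider 2–4 clusters, and the distribution of the clusters will be inspected visually". The last step is: "After the identification of the clusters, we will compare the pathophysiological characteristics between the clusters".

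For aims 2 and 6 the same section says openly that the statistical strategy cannot be settled yet. Aim 3 carries no such reservation, so its method is presented as decided.

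**The concern.** The task described is unsupervised: find groups that nobody has defined beforehand, in a number between two and four, then describe how they differ. The method named belongs to the opposite family. K-nearest neighbor takes patients whose group is known and uses them to assign a patient whose group is not.

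Two features of the text do not fit that method. Aim 3 supplies no known groups to learn from, and the only number given is a number of clusters, which is not what K means in K-nearest neighbor.

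At stake is whether the method behind a primary objective is fixed in advance. If the named method does not do the task, the analyst must substitute another one. Different clustering algorithms can group the same patients differently. If the choice is made with the data in view, the resulting classification can no longer be described as coming from a prespecified procedure.

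**Working it through.** No sample size, power or alpha figure bears on this point, and there is no stated figure to reproduce. The target of 500 cases and 500 controls is context only. The check sets what the method needs against what the text supplies.

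1. **Labels.** K-nearest neighbor needs patients with known group membership. Under aim 3 the clusters are identified first and pathophysiological characteristics compared afterwards. No labelled set is mentioned.

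2. **Could aim 2 supply labels?** Under aim 2, images of about 20% of patients are reviewed to set criteria, which then classify the other 80%. Of 500 cases that would be 0.20 × 500 = 100 and 0.80 × 500 = 400. Aim 3 does not use these classes to form its groups; pathophysiology enters only after the clusters exist. Aim 2 therefore does not rescue the wording.

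3. **Meaning of K.** In K-nearest neighbor, K is the number of neighbors consulted. The protocol's range of 2–4 is a number of clusters. A small illustration on assumed data (500 simulated patients, five standard normal variables, one data set per row; groups separated along one variable) shows that the two are different quantities. Each patient was linked to its k nearest neighbors and the separate linked sets were counted:

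| Simulated data | k=1 | k=2 | k=3 | k=4 | k=5 | k=10 |
|---|---|---|---|---|---|---|
| One homogeneous cloud | 123 | 1 | 1 | 1 | 1 | 1 |
| Three groups, 3 SD apart | 126 | 2 | 1 | 1 | 1 | 1 |
| Three groups, 8 SD apart | 119 | 3 | 3 | 3 | 3 | 3 |

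A neighbor count of 2, 3 or 4 did not give 2, 3 or 4 groups. K-means with K set to 2, 3 and 4 returned exactly 2, 3 and 4 groups in all three data sets, because there K is the number of clusters by definition. This shows only what each K controls. Linked sets are one crude graph method, and the illustration does not rank methods for PREVENT.

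4. **What remains specified.** With K-nearest neighbor set aside, the text fixes the range of cluster numbers and visual inspection. It fixes no rule that assigns patients to clusters.

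**The case against.** The strongest reply is that the text says clustering, not classification, and that unsupervised clustering on a nearest-neighbor graph is an established family. In a simulation on assumed data (40 data sets of 500 patients, two true types), spectral clustering on a 15-nearest-neighbor graph of standardised variables, without labels, returned exactly 2, 3 and 4 groups when asked. Its agreement with the true types was an adjusted Rand index of 0.77, against 0.78 for k-means on standardised variables. This stands. A reader might infer that the aim cannot be carried out by anything resembling the phrase used, and that is too strong. But such a method has two settings, the number of neighbors (15 there) and the number of clusters, plus a rule for partitioning the graph. The protocol names no such method and gives only the number of clusters.

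A second reply is that the phrase is a slip for k-means, which would fit the range of 2–4. That may be so, but the document does not say it. A reader might go further and infer that the analysis will be k-means on raw variables, with groups driven by age or stroke severity. The documents do not support that: they name neither k-means nor unscaled inputs. The list under Design that begins "age, sex, pre-stroke modified Rankin Scale (mRS), pre-stroke anticoagulation or platelet therapy" describes what the registry collects, not what enters the clustering. In the same simulation setting, standardised k-means did as well as a mixture model for mixed data (0.78 each). No case against the protocol can be built on k-means performance.

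A third reply is that an article leaves detail to the full protocol or analysis plan. That covers the choice of input variables and their scaling, whose absence is not criticised here. It does not cover an algorithm that the article does name and that does not match the task.

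Finally, aim 3 is data-driven and descriptive, and its study question is posed openly. This stands and limits the severity.

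**Conclusion.** The method is misnamed, and as written the sentence does not specify how the two to four clusters are to be obtained. This is a misstatement in the text, not an omission that an analysis plan would be expected to fill.

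It should be fixed, but its reach is limited. It affects aim 3 and whatever the expert panel under aim 6 takes from it. Aims 1, 2, 4 and 5 do not use the method, and eligibility, data collection and sample size are untouched. No numerical effect on the trial's results can be given, because neither the intended algorithm nor the clustering inputs are stated.

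The conclusion rests on the usual meaning of K-nearest neighbor and on the absence, in the article, of any labelled groups for aim 3 or any named graph-based clustering method. If a full protocol or analysis plan already names the algorithm, only the article's wording needs correcting.

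**What to change.** Before analysis, replace the phrase with a named unsupervised algorithm that can handle the registry's mix of continuous, ordinal and categorical variables. Two suitable choices are partitioning around medoids on Gower distance and a latent class or finite mixture model. K-means on standardised variables is acceptable only if the chosen inputs suit it. If clustering on a nearest-neighbor graph was meant, name that method and state the number of neighbors separately from the number of clusters.

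In the same sentence, state how the choice among two, three and four clusters will be made in addition to visual inspection, for example by silhouette width for a distance-based method or BIC for a mixture model.

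K-nearest neighbor may be kept only as a later step, to assign further patients to groups already defined.

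The cost is one sentence and minor analysis work, with no new data or patients.
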